Intramuscular (IM) glucocorticoid injection could be a valuable alternative treatment for IA glucocorticoid injection for patients with knee OA. IM administration eliminates the risk of septic arthritis and direct cartilage toxicity. The favorable effect of IM glucocorticoids on musculoskeletal pain has been studied originally in patients with rotator cuff disease and is used for rheumatoid arthritis [16, 17]. In a recent study from our study group, a clinical relevant and statistical significant difference in pain reduction was found for IM glucocorticoid injection compared to placebo in patients with hip OA [18]. Remarkably, the clinically relevant effect of the IM injection lasted at least 12 weeks. As of now no direct comparison between the effectiveness of IM and IA glucocorticoid injection in knee OA has been made.

We will perform a randomized controlled two-parallel-groups trial in patients with knee OA included from general practices, assessing the non-inferiority of an IM gluteal glucocorticoid injection compared to an IA glucocorticoid knee injection at 4 weeks follow-up. We hypothesize that IM gluteal glucocorticoid injection is non-inferior to IA glucocorticoid injection in reducing knee pain 4 weeks after injection, with potentially a longer lasting effect for at least 12 weeks.

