**Fig. 2 Fig2:**
[figure not shown]
Ventrogluteal intramuscular and superolateral intra-articular injection techniques

The IM injection will be administered in the ventrogluteal region (the region between the iliac crest, greater trochanter of the femur and anterior iliac spine, see Fig. 2a) in order to prevent injury to the sciatic nerve [29, 30]. Moreover, administration in the ventrogluteal region diminishes the possibility of subcutaneous injection in overweight patients since the layer of subcutaneous fat is less thick in the ventrogluteal region compared to the dorsogluteal region [31]. It is well known that knee OA is more common in patients with a BMI > 27 kg/m^2^ [32].

Co-interventions are allowed during the follow-up and will be monitored.

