### Data analyses

Imbalance in the baseline variables of the two treatment arms might occur after randomization. This is problematic if the imbalanced variable is related to the outcome variable, as this could lead to confounding [44, 45]. In case imbalance occurs, we will adjust for relevant variables. Descriptive statistics will be used to describe patients’ and complaints characteristics at baseline. Analyses will be adjusted for variables that hamper the baseline interchangeability of groups when there are clinically relevant differences between groups of over 10%.

The primary outcome is patient reported severity of pain at 4 weeks after injection measured with the KOOS pain (0–100; 0 = extreme pain). We will use a non-inferiority design to assess if an IM gluteal injection is non-inferior to an IA knee injection with regard to this outcome. In non-inferiority comparisons intention-to-treat analysis can bias towards the null and could increase type I error; the risk of falsely claiming non-inferiority [46]. Therefore, the per-protocol analysis will be the primary analysis. Included in the per-protocol analysis will be patients who received the assigned injection and reported the KOOS pain at 4 weeks follow-up. In case a patient from the IM injection group receives an additional IA injection earlier than 6 weeks after the study injection, this will be considered as a protocol violation and the patient will be excluded from the per-protocol analysis. The reason for this is that the guideline from the Dutch College of General Practitioners recommends to leave at least 6 weeks between two consecutive injections [6]. Non-inferiority of the IM injection will also be assessed using both intention-to-treat and per-protocol analysis at 2, 8, 12 and 24 weeks follow-up and for the outcome KOOS pain. For the other outcome measures we will calculate mean differences.

We expect 10–15% of missing data (incompletely filled in paper questionnaires and loss to follow-up). We will contact the patients to pose them the missing questions again in order to minimize missing data for the primary outcome. Multiple imputations will be performed for missing values (incompletely filled in questionnaires), creating at least five imputed datasets.

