Linear mixed models with repeated measures will be used to calculate group differences over time for the primary outcome as this is a continuous variable. To model the covariance of repeated measures by patients, a structure will be chosen with the lowest Akaike’s information criterion. Fixed effects will be time, and time by treatment.

Linear mixed models with repeated measures will also be used for the continuous secondary outcomes: KOOS, NRS, WOMAC, ICOAP, and EQ-5D-5 L. Generalized estimating equations analyses with repeated measures will be performed for the dichotomous outcomes: patients’ perceived recovery (7 point Likert scale), and the OMERACT-OARSI responder criteria. Before generalized estimating equations analyses, multiple imputations will be performed for missing values of secondary study parameters, creating at least five imputed datasets.

When patients underwent a total knee replacement surgery, data of these patients will be included up to the date of surgery. Missing data for secondary outcome measurements will be handled similarly as missing data for the primary outcome.

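### The per-protocol set is defined around week 4 but reused at weeks 8, 12 and 24, so it does not protect those non-inferiority assessments against dilution by later injections

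*Protocol article*

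**What the plan says.** All of the following is in the protocol article.

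- **Who is in the per-protocol set (Data analyses):** "Included in the per-protocol analysis will be patients who received the assigned injection and reported the KOOS pain at 4 weeks follow-up". The one injection-related exclusion applies to the IM arm: a patient who "receives an additional IA injection earlier than 6 weeks after the study injection, this will be considered as a protocol violation". The cut-off is justified by a guideline that "recommends to leave at least 6 weeks between two consecutive injections", not by the visit being analysed.
- **Why per-protocol is primary (Data analyses):** "In non-inferiority comparisons intention-to-treat analysis can bias towards the null and could increase type I error".
- **Later visits (Data analyses):** "Non-inferiority of the IM injection will also be assessed using both intention-to-treat and per-protocol analysis at 2, 8, 12 and 24 weeks follow-up". No separate set is defined for these visits.
- **Later treatment is foreseen:** the Intervention section says "Co-interventions are allowed during the follow-up and will be monitored", and Table 2 schedules re-injection with glucocorticoid as a secondary outcome at 8, 12 and 24 weeks.
- **The only truncation rule (Data analyses):** "When patients underwent a total knee replacement surgery, data of these patients will be included up to the date of surgery". There is none for a further injection.
- **What rests on the later visits (Background):** the hypothesis adds to week-4 non-inferiority an IM effect "with potentially a longer lasting effect for at least 12 weeks".

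**The concern.** A 6-week cut-off serves a week-4 endpoint well, because nothing that happens after week 6 can reach it. Three of the four additional non-inferiority visits fall after that cut-off. An IM patient given an IA knee injection in week 7 breaks no stated rule, stays in the per-protocol set, and contributes post-IA scores as IM outcomes at 8, 12 and 24 weeks. The same scores are in the intention-to-treat set.

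The article prefers per-protocol because treatment mixing pulls the arms together and makes a false claim of non-inferiority easier. At the later visits its per-protocol set does not remove the most direct form of that mixing. A reader who sees the two sets agree would take this as corroboration, although both carry the same contamination. What is at stake is the durability claim: if the IM effect fades and patients then receive IA, convergence of the arms could be read as a lasting IM effect.

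**Working it through.** **Inputs from the Sample size section:** margin 7 KOOS points, SD 16, power 80%, alpha 5% (sidedness not stated), 65 per group.

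**Reproducing the plan's figure.** n per group = 2 × SD² × (z_alpha + z_power)² / margin².
- One-sided 5%: 2 × 256 × (1.645 + 0.842)² / 49 = 64.6, so 65. This reproduces, with power 80.2%.
- One-sided 2.5% gives 83, which does not. One-sided 5% is therefore used below.

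**Decision rule.** SE = 16 × √(2/65) = 2.81. Non-inferiority needs an observed IM deficit below 7 − 1.645 × 2.81 ≈ 2.4 points. If the expected deficit is d, P(declare) = Φ((7 − d)/2.81 − 1.645).

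**Effect of late crossover.** The article gives neither quantity needed, so both are assumed: c, the share of IM patients with a late IA injection, and g, their mean KOOS gain at the visit. With IM truly 7 points worse and no IA-arm re-injection, d = 7 − c × g. For example, c = 10% and g = 10 give d = 6 and Φ(1/2.81 − 1.645) = 9.9%. Without crossover the rate is 5.0%.

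| c | g = 5 | g = 10 | g = 15 |
|---|---|---|---|
| 5% | 6.0% | 7.1% | 8.4% |
| 10% | 7.1% | 9.9% | 13.3% |
| 20% | 9.9% | 17.6% | 28.2% |
| 30% | 13.3% | 28.2% | 48.3% |

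**Allowing re-injection in both arms** (g = 10 in each), d = 7 − 10 × (c_IM − c_IA):
- 10% and 10%, or 20% and 20%: 5.0% (cancels)
- IM 20%, IA 10%: 9.9% (inflated)
- IM 10%, IA 20%: 2.3% (reversed)

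**A larger true deficit.** Suppose IM is truly 8 points worse and crossover brings a patient to the IA level, so d = 8 × (1 − c). The chance of declaring non-inferiority is 2.3% with no crossover, then 4.3%, 7.6% and 12.6% at 10%, 20% and 30% (d = 7.2, 6.4 and 5.6).

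These are simple two-group calculations. They ignore the repeated-measures model and any loss from the set. At week 8 only injections given between weeks 6 and 8 count, so a given c is more plausible at 12 and 24 weeks.

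**The case against.** **Direction.** A reader might infer that the later assessments are biased toward non-inferiority as a matter of course. The documents do not support that. Re-injections in the IA arm also stay in both sets, and Table 2 does not restrict the re-injection outcome to one arm. The Background describes IA relief as confined to about 1 to 6 weeks and hypothesises a longer IM effect; on that expectation re-injection could be commoner in the IA arm, and the bias would run against IM. This stands, and the conclusion must be conditional. What remains is that false non-inferiority is a risk only when IM is truly worse, and more rescue in the IM arm is then the expected pattern.

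**Size.** It is also tempting to reason that a true deficit of 8 diluted to 6.4 or 5.6 lies inside the margin, so non-inferiority would be declared. It would not, as a rule: the decision rests on the confidence bound, and even at 30% crossover the chance is 12.6%. This stands too.

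**Relevance.** Week 4 is untouched, later visits are secondary, and the lasting effect is worded only as a possibility. This limits the severity. It does not make the later per-protocol analyses sound.

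**Pragmatic design.** Co-interventions are permitted, a later injection respects the guideline spacing, and knee replacement is a different kind of event. This fully justifies keeping these patients in intention-to-treat. It does not give the per-protocol set a distinct purpose at weeks 8 to 24.

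**Already covered.** Re-injection is collected, and comparisons of co-interventions and medical consumption are planned. A sensitivity analysis might also sit in an analysis plan that is not shown. But the article itself fixes the set and the visits at which it is used, and that combination is the problem.

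**The remedy has its own bias.** After week 8, visits are 4 and then 12 weeks apart. A patient who worsens and is re-injected between visits leaves a last score from before the worsening, so a missing-at-random model may flatter the arm with more rescue. This stands and shapes the fix.

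**Conclusion.** The point holds in conditional form. At 8, 12 and 24 weeks the per-protocol set, as defined, gives no protection against dilution by injections at or after 6 weeks, and its agreement with intention-to-treat at those visits should not be read as reassurance. The bias can favour non-inferiority, cancel or reverse, depending on how often patients in each arm are re-injected and how much they gain.

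If IM is truly at the margin and only IM patients are re-injected, the false non-inferiority rate goes from 5% to about 7–13% at 10% late crossover and about 10–28% at 20%. These figures rest on assumed crossover shares, assumed gains of 5–15 points, 65 per arm, SD 16 and one-sided 5%.

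The documents do not support extending the point to the week-4 primary analysis. It is a change that should be made for the secondary assessments and for any durability claim.

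**What to change.** - **Per-protocol at 8, 12 and 24 weeks:** define the set by visit. Use KOOS pain only up to the first additional knee glucocorticoid injection in either arm and treat later values as missing. The same rule must apply to both arms.
- **Intention-to-treat:** leave as observed.
- **Reporting:** give the re-injection proportion by arm beside each later non-inferiority result.
- **Sensitivity analysis:** add one that does not assume missing at random after re-injection, for example carrying forward the unfavourable pre-injection or baseline level.
- **Interpretation:** claim a lasting IM effect only if these analyses agree.

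The cost is analysis-plan wording, one data step and one extra analysis. Re-injection is already scheduled for recording at the three visits; the team should confirm that the record identifies knee injections. The price is wider intervals at later visits and reliance on assumptions about scores after re-injection. This concerns the analysis only and implies no change to the clinical re-injection rule.

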### Subgroup analysis

An explorative, pre-defined, subgroup analysis will be performed assessing the interaction effects between injections regarding the severity of knee pain at baseline (NRS pain score of > = 7 versus < 7) on the primary outcome [47]. Generalized estimating equations will be used to analyze differences between groups concerning adverse events, medical consumption and medication usage.

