For patients who are selected via their electronic patient file, the actual amount of knee pain they experience is not known by their GP. These patients’ knee pain level will be checked over the phone by the researchers (given that the patient is willing to participate in the study, see Fig. 1). A minimum score of 3 on the numerical rating scale (NRS, 0–10; 0 = no knee pain) is required in order to participate in the trial. If a patient has an NRS knee pain score < 3, the patient will be asked to contact the research team in case of future increase in knee pain. In case a patient has bilateral knee OA, the most painful knee is selected as the ‘study knee’.

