***Additional measurements***							
Radiograph of study knee						x	
Check of ACR criteria		x					
Painfulness of injection (NRS)			x				
Demographic information	x						
Co-morbidity	x						
Physical activity over the past week (IPAQ short)	x						
Neuropathic pain (Modified painDETECT Questionnaire)	x						
Patients’ preferred injection site	x						
Patients’ expected treatment response	x						

Intermittent and constant OA pain will be measured with the Intermittent and Constant OsteoArthritis Pain score (ICOAP:0–100; 0 = no pain) [33]. Knee complaint characteristics (duration of symptoms at baseline, sensation of swelling in the knee as an indicator of flare-up) will be recorded. Knee pain severity averaged over the last week will be measured with an 11-point numerical rating scale (NRS:0–10; 0 = no pain). Health related Quality of Life (QoL) will be measured with the EQ-5D-5 L (scores ranging from − 0.446 = worst health related QoL to 1.0 = perfect health related QoL) [34, 35] Co-morbidity will be measured at baseline using a multiple choice format where patients can select multiple answers and add a missing comorbid disease. Also measured at baseline will be physical activity over the past week (IPAQ short), neuropathic pain (modified painDETECT questionnaire), patients’ preferred injection site (knee or ventrogluteal area) and patients’ expected treatment response [36, 37].

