### Sample size

For the sample size calculation, we used data from the study of Henriksen et al. that evaluated the clinical benefits of an IA glucocorticoid injection given before exercise therapy in patients with knee OA [40]. The results of the study reported a baseline standard deviation of 16 for the KOOS pain (recommended by the KOOS for sample size calculations is a standard deviation of 15). The minimal important difference (=non-inferiority margin) between both treatment groups of the patient reported outcome KOOS (0–100) was set at 7 points (effect size of 0.44) [41, 42].

For the non-inferiority of an IM gluteal glucocorticoid injection compared to an IA knee glucocorticoid injection, we will need 65 patients per group, using a power of 80%, an alpha of 5%, a non-inferior margin of 7 and a SD of 16. Taking into account a loss to follow-up of 5%, this trial needs to include (2*65) + (0.05*2*65) = ~ 140 patients. We expect a low percentage of loss to follow-up because of the relative short follow-up period of 24 weeks and our prior experience in glucocorticoid trials [18, 43].

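### The one pre-defined subgroup test reduces an 11-point baseline pain score to two groups, losing roughly 25–50% of the information on the interaction if the effect changes gradually with pain

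*Protocol article*

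**What the plan says.** The Subgroup analysis section of the protocol article states: "An explorative, pre-defined, subgroup analysis will be performed assessing the interaction effects between injections regarding the severity of knee pain at baseline". The outcome is the primary one, KOOS pain at 4 weeks. The modifier enters as two groups, "NRS pain score of > = 7 versus < 7", with a literature citation. No other subgroup analysis is described, and none that uses the score as a continuous modifier.

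The score itself is finer. Under Baseline measurements: "Knee pain severity averaged over the last week will be measured with an 11-point numerical rating scale (NRS:0–10; 0 = no pain". Under Patient selection: "A minimum score of 3 on the numerical rating scale (NRS, 0–10; 0 = no knee pain) is required in order to participate in the trial". Entry at 3 or above leaves eight possible values, 3 to 10.

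The Sample size section concerns the main comparison only: "we will need 65 patients per group, using a power of 80%, an alpha of 5%, a non-inferior margin of 7 and a SD of" (the value used there is 16). It gives no power for the interaction, and the article gives no expected share of patients at 7 or above.

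**The concern.** The split treats a patient scoring 3 like one scoring 6, and separates a 6 from a 7. If the IM versus IA difference drifts with pain severity, that discards information the trial already holds, in a sample sized for the main effect alone.

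This is the only effect-modification question the plan poses. A wide result from two groups could be misread as showing no difference by severity, and it rests on one cut-point. What is at stake is the precision and readability of an exploratory answer, not the trial's main conclusion.

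**Working it through.** **1. The plan's own figure.** The inputs from Sample size are the margin, "was set at 7 points (effect size of 0.44"), and the SD, "a baseline standard deviation of 16 for the KOOS pain". With one-sided alpha 0.05 and 80% power, n per group = 2 × 16² × (1.645 + 0.842)² / 7² = 64.6, so 65. The stated figure reproduces (one-sided 0.025 would need 83). Evaluable total: 2 × 65 = 130. With the 5% allowance, 130 × 1.05 = 136.5, rounded in the plan to about 140. The checks below use 130, because the 140 includes patients expected to be lost.

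**2. Information kept by the split.** Let X be the baseline score and H = 1 if X ≥ 7, otherwise 0. With 1:1 allocation and a treatment difference that changes linearly in X, the efficiency of testing treatment-by-H relative to treatment-by-X is corr(X, H)². The loss is 1 − corr(X, H)².

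A flat distribution on 3–10 can be done by hand. The variance of X is (8² − 1)/12 = 5.25. Half the patients are at 7 or above, with mean 8.5 against 6.5 overall, so cov(X, H) = 0.5 × (8.5 − 6.5) = 1. Then corr² = 1² / (5.25 × 0.25) = 0.76, a loss of 24%.

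For a normal distribution rounded to whole scores and truncated to 3–10 (mean and SD are those before truncation, and are assumed):

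| Mean | SD | Share at ≥7 | Information kept | Equivalent of 130 |
|---|---|---|---|---|
| 5 | 1.5 | 17% | 52% | 67 |
| 5 | 2.0 | 25% | 63% | 82 |
| 5.5 | 1.5 | 26% | 60% | 78 |
| 5.5 | 2.0 | 33% | 66% | 86 |
| 6 | 1.5 | 37% | 66% | 85 |
| 6 | 2.0 | 41% | 69% | 89 |
| 6.5 | 1.5 | 50% | 68% | 88 |
| 6.5 | 2.0 | 50% | 69% | 90 |

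Across this table 52–69% is kept, a loss of 31–48%. Adding the flat case gives a working range of roughly 25–50%. It is not a strict bound: if very few patients score 7 or more, the loss is larger (mean 4.5, SD 1.5 puts 10% at 7 or above and keeps 42%).

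**3. What this does to the test.** Take 130 patients, SD 16, a two-sided 5% test and share q at 7 or above. For the split, SE = 16 × √(4/(130q) + 4/(130(1 − q))).

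- q = 0.5: SE = 5.6. The interaction detectable with 80% power is 2.80 × 5.61 = 15.7 KOOS points. Power for a 7-point interaction is Φ(7/5.61 − 1.96), about 24%.
- q = 0.25: SE = 6.5, detectable interaction 18.2 points, power about 19%.

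For the continuous term, use a normal score and the linear slope that produces the same 7-point difference between the two group means. The slope per SD of X has SE = 2 × 16/√130 = 2.81. At q = 0.5 the group means are 1.596 SD apart, so the slope is 7/1.596 = 4.39, and power is Φ(4.39/2.81 − 1.96), about 35%. At q = 0.25 the gap is 1.695 SD, the slope 4.13, and power about 31%.

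The continuous term helps (24% to 35%, or 19% to 31%), but neither test has good power.

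**The case against.** The strongest reply is that the section contains no error. The analysis is labelled exploratory, is framed as an interaction test, and fixes its cut-point in advance with a citation. Pre-specification excludes the most serious danger of a split, a cut-point chosen from the data. How to model an exploratory modifier is partly preference, and the source of the cut is not shown, so its rationale cannot be judged here. All of this stands, and it limits how much weight the point can bear. It does not restore the information lost, and the change needs no new data.

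A reader might infer that the split costs at least a third of the information. The documents do not support that as a fact: they give no baseline pain distribution, several plausible distributions lose somewhat under a third, and the flat one loses 24%. The figure also requires a gradual interaction. If the effect steps at 7, the split loses nothing, and by the same squared correlation it is the linear term that would be the less efficient one.

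A reader might also infer that the split is why the subgroup question is underpowered. It is not the main reason. With 130 patients, power for a 7-point interaction is about 31–35% even with the full score, so sample size is the larger limit.

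**Conclusion.** The point holds as a minor, optional improvement. The plan's only effect-modification test reduces a 0–10 score to two groups. Under a gradual interaction this loses roughly 25–50% of the information, with 52–69% kept under the assumed rounded-normal distributions and 76% under a flat one.

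These sizes rest on three assumptions: the shape of the baseline distribution; a linear interaction; and the eligibility range of 3–10, set at screening, carrying over to the baseline score. The power figures also take SD 16 and 130 evaluable patients from the sample-size section; per-protocol exclusions would lower that number. The primary non-inferiority conclusion does not depend on this analysis.

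**What to change.** The Data analyses section specifies a repeated-measures linear mixed model with time and time by treatment as fixed effects. For the subgroup question, add baseline NRS as a continuous term with time-specific interactions: NRS by time, and NRS by treatment by time. Test the treatment-by-NRS interaction at week 4, and report the IM minus IA difference in KOOS pain with its confidence interval at selected scores, for example 4, 6 and 8. Keep the pre-specified comparison of 7 or above with below 7 as a secondary display, so that results can be set beside the cited work.

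This takes a sentence or two in the analysis plan and no new data, so it remains possible although the article reports recruitment as finished. It should be fixed before the analyst is unblinded. The downside is the assumption of approximate linearity: a quadratic interaction term can be examined, but with about 130 patients that check has little power.

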**Methods/design:**

The study will be a pragmatic randomized controlled non-inferiority trial with two parallel groups. A total of 140 patients aged 45 years and older with knee osteoarthritis who contacted their general practitioner and have persistent knee pain (score ≥ 3 on 0–10 numerical rating scale; 0 = no knee pain) will be included.

Patients will be randomly allocated (1:1) to an injection of 40 mg triamcinolone acetonide intra-articular in the knee joint or intramuscular in the ipsilateral ventrogluteal area.

The effect of treatment will be evaluated by questionnaires at 2, 4, 8, 12, and 24 weeks after injection. The primary outcome is patients’ reported severity of knee pain measured with the pain subscale of the Knee injury and Osteoarthritis Outcome Score 4 weeks after injection. Statistical analysis will be based on both the per-protocol and the intention-to-treat principle.

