## Background

The knee is symptomatically the most frequent affected joint in osteoarthritis (OA). In the Netherlands and other Western countries this is mainly managed by general practitioners [1]. The prevalence of knee OA in general practice was estimated around 40.2 per 1000 patient years (28.9 men; 51.4 women) in 2018 [2].

For OA patients, pain and disability are the most important reasons to seek care of a health professional [3–5]. If patients are not responding satisfactorily to paracetamol, NSAIDs and non-drug treatment, or in cases of interim aggravation, the evidence-based guideline from the Dutch College of General Practitioners on ‘Non-traumatic knee complaints’ suggests intra-articular (IA) glucocorticoid injection with 20 to 40 mg triamcinolone acetonide [6]. In several international guidelines IA glucocorticoid injection is also recommended for these abovementioned indications [7, 8].

Despite the long-standing frequent application of IA glucocorticoids, there is an ongoing debate about their effectiveness and safety [9, 10]. IA glucocorticoid injection in patients with knee OA leads to a moderate improvement in pain, but only in the short term (1 to 6 weeks after injection) [9]. IA injection has a small risk of the serious adverse reaction of septic arthritis on the short term [11]. In recent literature there is controversy over the chondrotoxicity of IA glucocorticoids on the longer term [12–14].

An additional obstacle in the way of IA injection is that GPs might feel incompetent to administer this type of injection due to lack of training and experience [15]. Due to the GP’s restraint, knee OA patients who could benefit from IA injection might not always receive timely injection [15].

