### Secondary objectives

The study will evaluate the differences in reported adverse events frequency and co-interventions of patients allocated to an IM gluteal glucocorticoid injection or to an IA glucocorticoid injection. Differences between the two treatment groups in several outcome measures related to knee recovery, on short and longtime follow-up (2–24 weeks) and quality of life will be measured (see Table 2).

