#### Follow-up measurements

Outcomes are measured at 2, 4, 8, 12 and 24 weeks after administration of the injection using digital questionnaires. Patients without an electronic mailbox will receive paper questionnaires. The primary outcome is patient reported severity of pain at 4 weeks after injection measured with the KOOS pain subscale (0–100; 0 = extreme pain). Secondary study endpoints are listed in Table 2. Patients’ perceived recovery is measured with a 7-point Likert scale that will be dichotomized in recovered (‘complete recovery’, ‘much improved’, ‘slightly improved’) and not-recovered (‘no change’, ‘slightly worse’, ‘much worse’,“worse than ever’) [18]. Percentage responders is defined by the OMERACT-OARSI criteria: High improvement (≥50%) in KOOS pain subscale or in KOOS function in daily living subscale and absolute increase ≥20 points in KOOS pain subscale or function in daily living subscale, if not then improvement in at least 2 of the 3 following domains: 1) ≥20% improvement in KOOS pain subscale and ≥ 10 points increase in KOOS pain subscale, 2) ≥20% improvement in KOOS function in daily living subscale and ≥ 10 points increase in KOOS function in daily living subscale, 3) ≥20% increase in global score and ≥ 10 points increase in global score. In this study patients’ global score will be measured with a patients’ perceived recovery score measured on a 7-point Likert scale. This domain is considered improved if a patient fills in ‘complete recovery’, ‘much improved’, or ‘slightly improved’ [38]. Two weeks after administration of the injection patients are asked to report adverse events. Also, follow-up questionnaires at all time points ask about hospitalization to monitor Serious Adverse Events. Co-interventions including medication, non-drug therapies such as physiotherapy, referrals and surgery will be measured with the modified medical consumption questionnaire of the Institute for Medical Technology Assessment (iMCQ) [39]. Experienced painfulness of injection will be registered 2 weeks after glucocorticoid injection. All data will be handled according to the Data Monitoring Plan, as drafted and approved by the funder in preparation of data collection.

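### GEE is named for adverse events without limit to common ones; with a logit link it gives no valid comparison for a harm seen in only one arm

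*Protocol article*

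**What the plan says.** The method is fixed in the last sentence under Subgroup analysis: "Generalized estimating equations will be used to analyze differences between groups concerning adverse events, medical consumption and medication usage". No link function, variance estimator or rule for sparse tables accompanies it. Under Data analyses, GEE is also the method for the dichotomous outcomes (perceived recovery and responder status).

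The comparison serves a stated aim. Under Secondary objectives: "The study will evaluate the differences in reported adverse events frequency and co-interventions".

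Adverse events are collected once. Under Follow-up measurements: "Two weeks after administration of the injection patients are asked to report adverse events". Table 2 agrees, with a single mark at 2 weeks. Hospitalization is a separate row of that table, asked about at all five follow-ups.

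The Background describes the main serious harm of the comparator: "IA injection has a small risk of the serious adverse reaction of septic arthritis on the short term". It then says of the intramuscular route: "IM administration eliminates the risk of septic arthritis and direct cartilage toxicity". Allocation is 1:1, and under Sample size: "we will need 65 patients per group".

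**The concern.** In a trial of this size, a specific uncommon harm will often appear in one arm and not in the other. For septic arthritis the article's own reasoning points to an empty intramuscular arm. A logistic model has no finite odds ratio for such a table. The software still prints numbers, and these depend on the variance option: one option makes a single chance event look overwhelmingly significant, and the other gives an interval without practical limits. Lower local harm is part of the case for the intramuscular route, so the comparison of specific harms should be readable. The single assessment at 2 weeks also means that there are no repeated adverse event measurements for GEE to model, so little is gained by using it there.

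**Working it through.** **Inputs.** Margin 7, SD 16, power 80%, alpha 5% and 65 per group are from Sample size. The event rates below are assumptions, because the article gives none.

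**Arm size.** n = 2 × 16² × (1.645 + 0.842)² / 7² = 64.6, so 65 per group, as stated (one-sided 5%). With about 140 enrolled, each arm has about 70. The pattern below is the same at 65 and at 70.

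**Why an empty arm breaks the logit model.** Let one arm have k events in n patients and the other none.
- The log odds in the empty arm run to minus infinity. The printed log odds ratio only shows where the iteration stopped.
- Model-based variance of the empty arm: 1/[n p̂(1 − p̂)], which grows without bound as p̂ goes to 0.
- Robust variance of the empty arm: n p̂² / [n p̂(1 − p̂)]², which goes to 1/n. The sandwich treats the empty arm as almost perfectly known.
- For 0 v 1 with n = 65, the robust variance is 1/1 + 1/64 + 1/65 = 1.031, so SE = 1.015 and z = 21.4/1.015 = 21.1.

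**Fitted logistic GEE, 65 per arm, one time point.**

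| Events | Log OR (absolute) | Robust SE; p | Model-based SE; p | Fisher p |
|---|---|---|---|---|
| 0 v 1 | 21.4 | 1.01 to 1.02; 1e-98 to 4e-100 | 44,172; 0.9996 | 1.00 |
| 0 v 3 | 22.5 | 0.59 to 0.60; 1e-304 or less | 44,172; 0.9996 | 0.24 |
| 0 v 5 | 23.1 | 0.47 to 0.48; 0 to machine precision | 44,172; 0.9996 | 0.058 |
| 1 v 3 | 1.13 | 1.17; 0.33 | 1.17; 0.33 | 0.62 |

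The small ranges depend on which arm is coded as reference. With 70 per arm, the same failure was seen with five time points and with exchangeable correlation. A bias-reduced sandwich did not repair it (1 v 0: p about 1e-96). The software reported convergence. Once both arms have events, as in the last row, GEE behaves normally.

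**How often this would produce a false difference.** With the same true rate p in both arms, the chance that exactly one arm of 65 is empty is 2q(1 − q), where q = (1 − p)^65. The rejection rates come from enumerating two Binomial(65, p) counts at a two-sided nominal 5%.

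| Assumed rate | Exactly one arm empty | Robust Wald test rejects | Fisher rejects |
|---|---|---|---|
| 1% | 49.9% | 49.9% | below 0.1% |
| 2% | 39.3% | 39.3% | 0.1% |
| 3% | 23.8% | 23.9% | 0.4% |
| 5% | 6.9% | 7.5% | 1.2% |
| 10% | 0.2% | 3.5% | 2.4% |

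At 1% to 3% the two middle columns nearly coincide, so the empty arm is the cause. By 10% the problem has gone.

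**What a score-based interval gives instead.** For 0/65 v 3/65 the Wilson limits are 0% to 5.6% and 1.6% to 12.7%. The risk difference is 3/65 = 4.6%. The Newcombe limits are 4.6 − √[(4.6 − 1.6)² + 5.6²] = −1.7% and 4.6 + √[(12.7 − 4.6)² + 0²] = 12.7% (computed before rounding).

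**The case against.** The strongest reply is that the failing model is only one reading of a short sentence. The article names GEE but no link. With an identity link, 0/65 v 1/65 gives z = 1.01 and p = 0.31, and the Wald test rejects 0.4%, 2.4%, 4.4% and 6.2% of the time at rates of 1%, 2%, 3% and 5%. This stands as a limit on the claim. It does not remove it, because a logit link is the usual choice for a binary outcome.

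A second reply is that the article has one row for adverse events and speaks of their frequency, so the planned comparison may be patients with any event. If such events are common, GEE is acceptable. This also stands. However, the sentence sets no such limit, and the harms that the Background names are specific ones.

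A third reply is that link, variance type and sparse-data rules belong in an analysis plan that is not shown. Those details as such are no finding. The point is that a method is positively assigned to an outcome that is measured once and will be sparse for specific harms, where a simpler method is better.

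Finally, a log odds ratio of about 21 beside counts of 0 and 1 would catch most readers' eyes. That lessens the practical risk, but leaves the choice of replacement until after the data are seen.

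**Conclusion.** The point holds in a limited form and is minor. With a logit link and 65 to 70 patients per arm, the named method gives no valid comparison for any adverse event confined to one arm. The size depends on assumed rates: false rejection of 50% to 24% at rates of 1% to 3%, 7.5% at 5% and 3.5% at 10%.

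Three stronger readings are tempting, and the documents do not support them.
- A reader might infer that the whole adverse event analysis fails. It does not: a comparison of common events works, and an identity link stays finite.
- A reader might infer that GEE is prescribed for serious events. Hospitalization is a separate item in Table 2 and is not listed in the sentence that names GEE, so this would be an inference.
- A reader might apply the 50% figure to septic arthritis. That figure assumes equal rates in both arms, whereas the Background expects no such risk in the intramuscular arm and gives no rate for the other. For that harm, only the empty-arm failure itself is relevant.

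The primary outcome, its margin and the sample size are untouched.

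**What to change.** Under Subgroup analysis, limit GEE to the repeated outcomes, medication usage and medical consumption. For adverse events, state that the number and percentage of patients with at least one event will be reported per arm, overall and by type, with the risk difference and a Newcombe or other score-based 95% confidence interval, and Fisher's exact test if a test is wanted.

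This costs one sentence and no new data. The small downside is that exact tests are conservative and give no covariate-adjusted odds ratio.
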